**Table 1. Internal Pilot progression criteria**

| **Progression criteria** | **Red** | **Amber** | **Green** |
| --- | --- | --- | --- |
| **% Threshold** | <74% | 75-99% | **100%** - all below criteria must be met to proceed directly to main recruitment phase. |
| **Recruitment rate/site/month** | ≤ 0.74 participants per month per site | 0.75 to 0.99 participant per month per site | ≥ 1.0 participant per month per site |
| **Number of sites opened by the end of the pilot phase** | ≤ 6 | 7 to 9 | ≥10 |
| **Total number of participants recruited** | ≤ 44 across all pilot sites over 6 months | 45 to 59 across all pilot sites over 6 months | ≥ 60 across all pilot sites over 6 months |

### Qualitative research by QuinteT

We will optimise recruitment with the inclusion of a QuinteT Recruitment Intervention (QRI) led by qualitative experts (based at the University of Bristol). The overarching aim of the QRI is to support recruitment to EVOCC. Initially, the QRI team will share existing knowledge of approaches that help with information delivery and trial conduct. Thereafter, it will employ the QRI methodology: a mixed-methods approach that has been implemented in over 30 RCTs to optimise recruitment and informed consent (52). The QRI employs qualitative and mixed-method approaches to understand recruitment issues rapidly (Phase 1), and then uses this evidence to design and implement tailored strategies to optimise recruitment processes (Phase 2). The QRI will be integrated in the pilot phase and learning from this will be transferred to the main RCT. Further information on Phase 1 and Phase 2 can be found below.

**Phase 1: Understanding recruitment**

Phase I aims to understand trial recruitment processes and how these may differ across participating sites. It will specifically aim to support staff in overcoming challenges in recruiting participants from certain minorities, deprived backgrounds, and those who are frail. A multi-faceted, flexible approach will be employed, including one or more of the following:

1. Semi-structured interviews with: (i) members of the TMG (ii) clinicians or researchers involved in trial recruitment (‘recruiters’) (n=10-25), and (iii) eligible patients who have been approached to take part in the trial (n=5-15). Interviews with members of the TMG and recruiters will focus on: their perspectives on the evidence upon which the trial is based; perceptions of uncertainty/equipoise; views on the appropriateness of eligibility criteria, and (where relevant) experiences of recruitment difficulties or successes. Interviews with patients will explore views on the presentation of trial information, understandings of trial processes (e.g., randomisation), and reasons underlying decisions to accept or decline the trial. Patients will be purposefully sampled, to build a sample of maximum variation based on age, gender, trial centre, and their decision about trial participation (i.e., accept or decline). Interviews will be conducted via telephone or a secure web-conference facility (e.g., Skype, MS Teams, Zoom or Google Hangouts), where conducting these in person is not feasible.
2. Analysis of audio-recorded recruitment discussions: ‘Recruitment consultations’ between recruiters and potential participants will be audio-recorded with permission. This will be a core aspect of data collection, as it allows an opportunity to investigate actual (rather than perceived) recruitment behaviours. The audio recordings will be used to examine how the trial treatments and trial processes (e.g., randomisation) are explained to patients, how equipoise is conveyed, and how patients react to the information provided. Audio-recordings of recruiter-patient consultations do not require the presence of a researcher. If recruitment consultations need to be conducted remotely via telephone due to COVID-19 or other restrictions, equipment will be provided to allow the recruiters to audio-record their telephone calls with patients (upon receipt of appropriate consent).
3. Scrutiny of trial screening logs and mapping of recruitment pathways: working in close collaboration with LCTU, a comprehensive screening log will be designed to capture numbers of patients screened, eligible, approached, randomised, and numbers accepting their randomised allocation. The logs and interviews (described above) will be used to construct flow charts depicting the ‘recruitment pathway’ for each centre, and the points at which patients enter/exit the pathway. Numbers captured in the screening logs will be compared across centres and considered in relation to estimates specified in the grant application/trial protocol. This process will be regularly repeated to identify bottlenecks in the recruitment pathway and inform further data collection through interviews and/or analysis of consultations.

**Phase 2: Development and implementation of recruitment intervention strategies**

Working closely with the CI and TMG, a ‘plan of action’ will be formulated, consisting of specific strategies designed to improve recruitment and informed consent processes. The plan will be informed by Phase 1 evidence and is likely to include generic and site-specific interventions. Generic interventions may include written guidance documents that provide suggestions on how to explain the trial to patients in a balanced way (i.e. conveying equipoise). Supportive feedback will feature heavily in the plan of action, with the precise nature and timing dependent on the issues that arise. For example, feedback may be offered to individual centres, through multi-centre feedback or confidentially to individual recruiters. All feedback will be supported with anonymised data extracts from interviews and recruitment consultations.

Although the QRI has been presented as two distinct phases for clarity, the phases will overlap. New avenues of enquiry will arise as data collection proceeds and new centres open, and the feedback sessions themselves may highlight new issues that warrant further investigation. Screening logs will be assessed throughout the recruitment period, with particular scrutiny of figures before/after Phase 2 interventions are implemented. This will help to inform decisions about further investigation or intervention throughout the trial’s recruitment period.

**QRI consent processes**

Healthcare professionals (HCPs) involved in the EVOCC trial recruitment will receive a copy of the ‘QRI healthcare professional information sheet’ at Site Initiation Visits (SIVs) or via email from the QRI researcher. This will explain the QRI processes described above (specifically, audio-recording of recruitment discussions and interviews). Research nurses or the QRI researcher will obtain written consent from HCPs using a consent form. HCPs may opt to participate in just one, both, or neither of the QRI elements.

Patients will also receive a ‘QRI Participant information sheet’ (PIS) explaining the audio-recording of recruitment discussions and the possibility of being approached for a future interview. The PIS will be handed to patients during the first discussion about the RCT. As we wish to capture how the RCT is introduced to patients, we will employ a two-step consent process for audio-recording recruitment discussions. In brief:

- A member of the clinical team (who by default, may also be a member of the research team) will obtain verbal consent to record the initial discussion about EVOCC. If patients agree, the ‘verbal consent form’ will be signed by the HCP to document that verbal consent has been obtained, and the discussion will be recorded.
- Patients will receive the QRI PIS in the first consultation, and will be provided sufficient time to ask any questions and consider their participation in the QRI.
- Patients will be asked to provide written informed consent for the audio-recordings and/or interviews in their subsequent baseline visit. Further RCT recruitment discussions will be audio-recorded subject to receiving written consent; if written consent is not obtained, the recording captured from the first discussion will be deleted (if collected) and no further recordings will be made.

Patients can accept or decline participation in the audio-recordings, interviews, or both. Their decision(s) about QRI participation will be independent to their decision about RCT participation.

A verbal consent process will also be employed to reduce burden on HCP participants, where obtaining consent in person is problematic (e.g., due to lack of research nurse capacity). Potential participants will be sent a copy of the study information sheet and consent form via email. The QRI researcher will call the HCP and read each statement on the consent form, initial these as is appropriate, and sign to confirm they have obtained consent. The consent discussion will be audio-recorded and a copy of the completed form will be sent to the participant for their records. All QRI consent forms will be retained at sites.

In light of the COVID-19 pandemic, all of the consent processes for the QRI can be easily adapted to ‘verbal consent’ processes, whereby the individual taking consent reads the consent form statements and signs on the potential participant’s behalf. These discussions can be audio-recorded to provide a record of the potential participant confirming their consent. These verbal consent processes will likely take place irrespective of whether the consultation is taking place in person or remotely, in an effort to minimise risk of transmission (e.g., through use of pens, contact with paper, etc).

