A Participant Information Sheet (PIS) will be provided to facilitate this process. The Principal Investigator or their delegate will ensure that they adequately explain to the participant the aim, trial intervention, anticipated benefits and potential risks of taking part in the trial.

The participant will be given time to consider the information, and the opportunity to question the Investigator, their GP or other independent parties to decide whether they will participate in the trial. They will be given sufficient time, usually 24 hours, to make their decision. Written Informed Consent will then be obtained by means of participant dated signature and dated signature of the person who presented and obtained the informed consent. The person who obtained the consent must be suitably qualified and experienced, and have been authorised to do so by the Principal Investigator as detailed on the Delegation of Authority and Signature log for the trial. The original signed form will be retained at the trial site within the Investigator Site File (ISF). A copy of the signed Informed Consent will be given to participants and a copy retained in the participant medical notes. The outcome of the conversation, i.e., provided informed consent and have been randomised to the trial, will be recorded in the trial screening log. This will be necessary for assessing recruitment feasibility.

The ICF contains optional items relating to consent for the use of data held by central NHS bodies (see below) and the retention of contact information to enable future contact for consideration of participation in follow-up studies. Participants may provide or decline consent for any of these items independently. Should new and important information, particularly relating to safety, become available during the trial, participants may be required to re-consent to the trial via an updated PIS and ICF.

Once the participant is randomised onto the trial, their Participant ID Number will be populated and recorded on the ICF and all Case Report Forms (CRFs) going forward.

Details of the informed consent discussions should be recorded in the participant’s medical notes in accordance with Good Clinical Practice (GCP). This should include date of discussion, the name of the trial, outcome of the discussion, version number of the PIS given, version number of ICF signed and date consent received.

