## Randomisation

After the consent form has been signed, the participant will be randomised to receive one of the two arms; open surgery or endovascular treatment. Participants will be randomised via the 24 hour, web-based service, Sealed Envelope.

Random allocations will have a 1:1 ratio, will be minimised by the following variables: age above 65 years, sex, and presence of tissue loss (yes/no) and stratified by site. Randomisation forms should be completed alongside online randomisation. After a participant is randomised, the user is presented with the allocated treatment group and the unique Participant ID Number. A notification email will be sent to the person conducting the randomisation, copying in Leicester Clinical Trials Unit via the EVOCC trial mailbox. The Participant ID number must be entered onto the participant signed ICF and all CRFs from this point forward and will link the participant details to the trial data. Any errors in the randomisation process should be reported to Leicester Clinical Trials Unit as soon as reasonably possible after being identified.

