## Trial assessments

### Baseline Visit (Day 0)

Once a Participant ID Number is allocated, the Baseline visit can take place. During this visit, participants will complete participant questionnaires, undergo a review of their medical history (including previous surgical interventions), cardiovascular risk factors, PAD anatomy, eGFR, HbA1C, LDL and cholesterol levels. If a female is thought to be pregnant, a urine pregnancy test will be performed as part of usual care ahead of surgery. Where a female participant is found to be pregnant, progression to treatment will be assessed using a risk-based approach as managed routinely by the patient’s treating clinician. Baseline visit biochemistry assessments/bloods to be taken in line with clinical pathway and matching the research schedule as closely as possible. It is understood that because these bloods are clinical, that there may be occasions where these bloods are taken ahead of the research baseline timepoint. Please refer to **Table 2** for further details about the Baseline visit, follow up visits and assessments.

### Review of Clinical Events – Day of Discharge, Day 30 and Months 6, 12, 24, 36, 48 and 54

A review of clinical events, particularly those related to the cardiovascular system, will be undertaken at the above trial visits including re-intervention, admission to hospital, death, myocardial infarction, stroke and new heart failure leading to admission. For visits at day 30, months 12, 36, 48 and 54, data collection will be performed either by telephoning the participant or retrieving the information from their medical notes. For visit month 6, the participant needs to attend clinic in person. However, if the participant cannot attend in person, as this is a pragmatic study this information can instead be collected remotely via telephone or through acquiring information through participant medical records.

### Biochemistry Assessments – Baseline and Month 6

Standard blood sample assessments to be undertaken in clinic at Baseline and month 6 and should include eGFR, total cholesterol, LDL cholesterol and HbA1C - these are NHS standard of care and constitute part of these patients regular care as per NHS and National Institute for Health and Care Excellence guidance. The blood samples (5ml collected at each visit) will be collected at room temperature before being processed and analysed at the local pathology laboratories as per each site’s standard procedures for these patients.

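### Written QRI consent is tied to a baseline visit that, read literally, follows randomisation, so patients who decline the RCT have no point at which to give it

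*Protocol*

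**What the plan says.** Section 5.1.1 sets out a two-step consent for recording recruitment discussions. The first discussion is recorded on verbal consent, and the patient then receives the QRI information sheet. For the second step, the protocol says: "Patients will be asked to provide written informed consent for the audio-recordings and/or interviews in their subsequent baseline visit". The consequence of not reaching it is fixed: "if written consent is not obtained, the recording captured from the first discussion will be deleted", and no more recordings are made. Later recruitment discussions are to be recorded once written consent is in place. The same section adds: "Their decision(s) about QRI participation will be independent to their decision about RCT participation".

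Phase 1 of the QRI says what the data are for. Patient interviews are to explore "reasons underlying decisions to accept or decline the trial", and the 5 to 15 interviewees are to be sampled partly on which decision they made.

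The timing of the baseline visit is set elsewhere. Section 8.4.1 says: "Once a Participant ID Number is allocated, the Baseline visit can take place". Section 8.3 says: "After a participant is randomised, the user is presented with the allocated treatment group and the unique Participant ID Number". Section 8.2 agrees: "Once the participant is randomised onto the trial, their Participant ID Number will be populated and recorded on the ICF". Table 2, however, lists the eligibility check, RCT consent and randomisation in the Baseline column at Day 0.

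**The concern.** If the baseline visit comes after randomisation, the only stated point for written QRI consent comes after the decision that the QRI is meant to explain. A patient who declines the RCT has no baseline visit and so is not asked. The recording is then deleted because no consent is on file, although the patient never refused the QRI.

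The material at stake is recorded consultations, which the protocol calls a core part of its data collection, and patient interviews. Both would come from acceptors only, so this evidence would be selected on the outcome under study. It also feeds the advice given to recruiters during a pilot whose recruitment targets can stop the trial. Section 8.6 confines formal qualitative assessment to the pilot, so decliner data lost there may not be recoverable later.

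**Working it through.** The point concerns the order of events, so the main check sets the sections side by side.

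**Literal sequence (sections 5.1.1, 8.2, 8.3, 8.4.1)**
1. First discussion, recorded on verbal consent.
2. RCT consent.
3. Randomisation, which issues the Participant ID.
4. Baseline visit, where written QRI consent is sought.
5. No written QRI consent: first recording deleted.

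A decliner leaves at step 2 and never reaches step 4, so step 5 applies by default. This conflicts with three statements in section 5.1.1: the sampling of decliners as well as acceptors, the independence of the QRI and RCT decisions, and the recording of more recruitment discussions after written QRI consent. On this sequence nothing is left to recruit for once that consent is given.

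**Table 2 sequence**
1. First discussion, recorded on verbal consent.
2. Patient attends Baseline, where RCT consent, randomisation and (by section 5.1.1) written QRI consent all fall.

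Here a patient can attend, agree to the QRI and decline the RCT. The statements in section 5.1.1 then fit together, but section 8.4.1 is contradicted. A gap also remains. Section 8.1 lets the trial information go by post or e-mail, and section 8.2 gives patients time, usually 24 hours, to decide. A patient who says no in that interval does not attend Baseline under either sequence.

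**Does the verbal alternative close the gap?** Section 5.1.1 allows all QRI consent processes to become verbal, in person or remote. It changes the form of consent. It names no time point and does not lift the deletion rule.

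**Can the number affected be worked out?** The only related figure is the 6% consent rate in section 11.2.
- Inputs from section 11.2: 2,200 open and 4,000 endovascular eligible procedures a year, about 30 networks, and a target of 1 participant per site per month.
- Eligible per site per month: (2,200 + 4,000) / 30 / 12 = 17.2.
- Implied rate: 1 / 17.2 = 5.8%, which reproduces the stated 6%.
- Pilot target: 10 sites × 6 months × 1 = 60 participants.
- Eligible in the pilot: 60 / 0.06 = 1,000, or 60 × 17.2 = 1,033 unrounded.
- Not randomised: 1,000 − 60 = 940, or 1,033 − 60 = 973, which is 94% either way.

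That 94% includes everyone eligible who is not randomised, most obviously those never approached. The protocol does not say how many will be approached, how many of those will decline, or how many first discussions will be recorded. It is an upper bound on the share lost, and reaches that bound only if every eligible patient is approached and recorded.

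**The case against.** The strongest reply is that section 5.1.1 plainly intends to include decliners. It samples them, separates the two decisions and expects recruitment discussions to continue after QRI consent. Section 6.2 does not require randomisation for patients in the communication study. With Table 2, this suggests that the author of section 5.1.1 had in mind a visit that precedes or contains the RCT decision. The consent steps are also given only in brief, and the separate QRI information sheets and consent forms are not at hand. Much of this stands: the protocol is inconsistent about the baseline visit and does not set out a deliberate exclusion. The intention, however, does not supply a consent point. Section 8.4.1 is explicit, and patients who decline before attending are missed on either reading.

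A reader might infer that the QRI cannot find out why patients decline. The documents do not support that. Phase 1 also includes 10 to 25 recruiter interviews covering recruitment difficulties, and screening logs that map where patients leave the pathway. Neither depends on patient QRI consent, so feedback to recruiters would not rest on successful consultations alone.

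A reader might also infer that about 94% of first recordings would be deleted. That treats recruits divided by eligible procedures as a refusal rate, which it is not.

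**Conclusion.** The concern holds as a contradiction with a practical consequence. Sections 5.1.1 and 8.4.1 and Table 2 cannot all be followed as written. On the literal sequence, all RCT decliners lack a point at which written QRI consent is sought. On the Table 2 sequence, those who decline before attending still lack one. The result is loss of their recordings and interviews, the most direct evidence on declining.

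The size cannot be given, because the documents state neither the number approached nor the refusal rate among them. The direction of the selection, towards acceptors, does not depend on either. The conclusion assumes that the unseen QRI forms do not set another consent point. The effect is confined to the qualitative recruitment work: the primary outcome, its analysis and the sample size are untouched. The point is worth correcting because the change is small and protects a stated aim of the pilot.

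**What to change.** 1. In the section on QRI consent processes, replace the reference to the baseline visit with wording such as: *QRI consent, written or in the audio-recorded verbal form described below, will be sought before or at the time of the patient's decision about the RCT, or by remote contact afterwards, whether or not the patient joins the RCT.*
2. Reconcile that section, section 8.4.1 and Table 2 on whether RCT consent and randomisation come before the baseline visit or form part of it.
3. Keep the rule that the first recording is deleted if QRI consent is not obtained, and add a stated period, agreed with the ethics committee, within which consent must be obtained. Deleting only on an explicit refusal would weaken the present safeguard, because recordings of patients who never reply could be kept indefinitely on verbal consent alone.

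The verbal form already exists in section 5.1.1. The electronic and telephone routes in section 8.2 are for RCT consent, so using them for the QRI would have to be written in. The cost is an ethics amendment and one extra contact for some patients who decline.
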